### Participants and recruitment

Participants with PN caused by UTD1 will be recruited at Zhejiang Cancer Hospital between 1 September 2022 and 30 June 2024. Recruitment posters will be placed in the department of breast medical oncology to increase exposure.

### Inclusion criteria and exclusion criteria

All participants will be screened according to the inclusion criteria and exclusion criteria at the baseline (Table 2 for details).

**Table 2 T2:** Inclusion criteria and exclusion criteria.

**Patients who meet the following requirements will be considered for inclusion:**	**Patients will be excluded if they have:**
(1) Diagnosed as advanced breast cancer and PN symptoms occur after using UTD1. The patient had no obvious PN symptoms before using UTD1; (2) Over 18 and under 70 years old, and the expected survival time was ≥6 months; (3) Have daily living ability and can complete all questionnaire investigation; (4) No serious heart, brain, kidney, and other diseases, KPS score >70; (5) Clear consciousness without severe mental illness or cognitive impairment; (6) Sign the written informed consent form.	(1) Diagnoses as other severe systemic diseases (e.g., cardiovascular disease, acute infectious disease, hematopathy, et al.); (2) Diagnoses as severe mental disorders, like schizophrenia; (3) PN caused by other diseases, such as diabetic peripheral neuropathy; (4) Alcohol and/or other drug abuse or dependence; (5) Pregnant and lactating women; (6) Participating in other clinical trials.

PN, peripheral neuropathy; UTD1, Utidelone; KPS, Karnofsky performance status.

### Randomization and allocation concealment

The randomization will be performed by the Department of Scientific Research, Zhejiang Cancer Hospital. A randomization method will be used to generate the random allocation sequence of two groups in a ratio of 1:1; two groups of random serial numbers will be randomly placed in opaque, sealed envelopes by other staff who will not be involved in the study to ensure the concealment of distribution. These envelopes will be printed with consecutive numbers on the outside. The envelope with the corresponding serial number will be selected according to the participant's visit order.

### Blinding

Participants will be informed that they have a 50% chance of being assigned to receive either of the two treatments: the EA treatment or drug treatment. However, as there is a complete difference between the treatment methods of the two groups, the participants cannot be blinded. At the same time, although acupuncture doctors also cannot achieve blindness because of the need for treatment, they will not be involved in the assessments or data analyses. The follow-up data managers who collect data and outcome assessors will be unaware of the group allocation of the participants.

## Intervention

### The EA treatment group

The selection of acupoints is based on the experience of acupuncture experts and referring to previous literature on acupuncture treatment of CIPN, the high-frequency application acupoints are selected. The location standard of the acupoints is based on the WHO standard for acupuncture point location (25). The location of selected acupoints is shown in Table 3. Bilateral Quchi (LI11), Waiguan (SJ5), Houxi (SI3), Hegu (LI4), Baxie (EX-UE9), Taichong (LR3), Sanyinjiao (SP6), Yinlingquan (GB34), Yanglingquan (SP9), Zusanli (ST36), and Bafeng (EX-LE10) acupoints will be taken in the limbs. Upper limb EA will connect Quchi (LI11) with Waiguan (SJ5); lower limb EA will connect Sanyinjiao (SP6) with Yanglingquan (SP9). The EA frequency will be 2 Hz, and the stimulation intensity will be based on the patient's tolerance (no discomfort). The duration of each treatment will be 30 min, three times a week for 4 weeks.

**Table 3 T3:** Location of acupoints for treating PN caused by UTD1.

**Acupoints**	**Location**
Hegu (LI4, bilateral)	On the back of the hand, between the first and second metacarpals, at the midpoint of the radial side of the second metacarpal.
Houxi (SI3, bilateral)	Slightly clench the fist, the distal side of the ulnar side behind the palmar joint of the fifth finger, the horizontal pattern of the palm, and the red and white flesh border of the head.
Waiguan (SJ5, bilateral)	2 cun above the transverse crease of the dorsal wrist, the midpoint of the gap between ulna and radius.
Quchi (LI11, bilateral)	Bend the elbow at a right angle when the elbow bends at the end of the transverse line.
Baxie (EX-UE9, bilateral)	There are 8 points on the back of the hand, behind the edge of the web between the first and fifth fingers, between the red and white flesh, left and right.
Zusanli (ST36, bilateral)	3 cun below genicular eye of outside, one finger -breadth (middle finger) from the anterior crest of tibia.
Yanglingquan (GB34, bilateral)	On the outside of the lower leg, when the fibular head is in the depression before and below.
Yinlingquan (SP9, bilateral)	In the depression between the medial lower edge of the lower tibia and the medial edge of the tibia.
Sanyinjiao (SP6, bilateral)	3 cun above the medial malleolus, on the posterior border of the medial aspect of tibia.
Taichong (LR3, bilateral)	In the dorsum of the foot, between the first and second metatarsals, and in the depression in front of the metatarsal junction.
Bafeng (EX-LE10, bilateral)	Between the first to fifth toes, at the red and white flesh border behind the toe web edge, there are four acupoints on one side, with a total of eight acupoints on the left and right.

Equipment: the Huatuo brand disposable acupuncture needles produced by Suzhou Medical Instrument Factory will be adopted, with models of 0.25 ^*^ 40 MM. The Hans-200A model will be adopted as EA equipment.

### The control group

The participants will be treated with oral mecobalamin (MeCbl) tablets, one tablet (0.5 mg) each, three times a day for 4 weeks.

### Outcome measures

The severity of PN caused by UTD1 will be evaluated according to the evaluation scale of peripheral neurotoxicity of chemotherapeutic drugs according to EORTC QLQ-CIPN20, the peripheral neurotoxicity grades will be evaluated according to NCI CTCAE version 5.0, and the quality of life scale according to EORTC QLQ-C30 will be the outcomes used to evaluate efficacy and safety. Adverse events (AEs) will also be recorded to evaluate safety.

### Primary outcome

#### The evaluation scale of peripheral neurotoxicity of chemotherapeutic drugs according to EORTC QLQ-CIPN20

There are 20 items in the questionnaire, including 9 items in the subscale of sensory nerve symptoms (involving tingling, numbness, pain, walking or standing instability, temperature perception, and hearing), 8 items in the motor nerve symptom subscale (involving spasm writing, manipulation of small objects, and weakness), and 3 items in the autonomic nervous symptom subscale (involving vision, vertigo after changing posture, and erectile dysfunction) (26). The scoring method is the same as that of other QLQ scales. All items are scored with four levels: “no, a little, quite, and very,” respectively, assigned 1–4 points. After standardizing the scores of each dimension according to the scoring requirements, the score range of each dimension is 0–100 points. The higher the score, the more the severe CIPN symptoms. At present, the reliability and validity of the tool have been tested to a certain extent in some countries (27, 28), and it has been applied to corresponding studies (29, 30).

#### Peripheral neurotoxicity grades will be assessed according to NCI CTCAE version 5.0

This outcome will be determined by the professional evaluator according to the symptoms of PN in the patient, including checking the degree of peripheral nerve damage of the participant, such as muscle strength and muscle tension. In grade I, slight sensory numbness or tendon reflex disappeared, with no function affected. Grade II includes moderate sensory numbness or sensory loss, which affects function but does not affect daily life. Grade III includes significant sensory numbness or sensory loss, which affects daily life. Grade IV includes sensory-motor neuropathy, which severely interferes with daily life (31).

### Secondary outcome

#### The quality of life scale according to EORTC QLQ-C30

The European Organization for Research and Treatment of Cancer QLQ-C30 is a quality-of-life instrument for use in international clinical trials in oncology (32). QLQ-C30 scale includes five functional subscales, three symptom subscales, six single symptom measurement items, and one overall health subscale. The higher the functional subscale score, the better the quality of life, and the higher the symptom subscale score, the worse the quality of life.

### Safety evaluation

All AEs during the study will be recorded, including EA-related AEs (e.g., hematoma, dizziness, and nausea) and drug-related AEs (e.g., gastrointestinal discomfort and nausea). The AEs occurrence time, treatment process, result, follow-up, and whether the participant will continue to be included in the trial will be recorded. In addition, whether the patient's cancer condition develops and quality of life will also be considered safety evaluation indicators.

### Quality control

All acupuncture doctors and evaluators will be required to undergo special training before the trial to ensure consistent practices. The training contents will include the diagnosis of PN caused by UTD1, acupoints location, EA application technology, inclusion criteria, exclusion criteria, and evaluation criteria of case report forms. All the study data will be recorded in case report forms and entered into the electronic data capture system by independent researchers. Dropouts will be recorded throughout the trial.

This trial will be monitored by the Department of Scientific Research, Zhejiang Cancer Hospital. They will be responsible for monitoring the data and verifying the authenticity between the raw data and the recorded data to guarantee accuracy and quality throughout the study.

## Statistical methods

### Sample size

This is a prospective clinical study. According to the principles of the randomized controlled trial, the EA treatment group and the control group are designed, and 35 patients will be included in each group.

### Statistical analysis

The outcome data will be analyzed by the Statistical Package for the Social Sciences (SPSS) version 26.0 statistical software package. The researchers conducting data analysis will not know the distribution of participants and treatment methods. Categorical data will be displayed as counts and percentages. Numerical data of normal distribution will be expressed as mean ± standard deviations, while data of non-normal distribution will be expressed as median, minimum value, and maximum value of 95% confidence intervals. To compare the two independent samples, the *t*-test will be used to determine the numerical data of normal distribution, while the non-parametric test will be used to determine the data of non-normal distribution. The chi-square test or non-parametric tests will be used to determine categorical data. All hypothesis tests will be bilateral, with the level of significance established at 0.05.

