**Methods and analysis:**

This study is a prospective randomized controlled trial. A total of 70 patients with PN caused by UTD1 will be randomly assigned to the EA treatment group and the control group in a ratio of 1:1. The patients in the EA treatment group will receive 2 Hz EA three times a week for 4 weeks. The patients in the control group will take mecobalamin (MeCbl) tablets orally, one tablet each, three times a day for 4 weeks. The main outcome measures will be the evaluation scale of peripheral neurotoxicity of chemotherapeutic drugs according to the European Organization for Research and Treatment of Cancer Quality of Life Questionnaire-CIPN 20-item (EORTC QLQ-CIPN20) and the peripheral neurotoxicity assessment rating according to NCI CTCAE version 5.0. Secondary outcomes will be the quality of life scale according to the European Organization for Research and Treatment of Cancer Core Quality of Life Questionnaire (EORTC QLQ-C30). The results will be evaluated at baseline, post-treatment phase, and follow-up. All major analyses will be based on the intention-to-treat principle.

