### Study design

The trial is designed as a prospective, randomized, controlled, and blind study to compare the therapeutic effects of EA therapy on PN caused by UTD1. A total of 70 participants with PN caused by UTD1 will be randomly divided into two groups in a ratio of 1:1, which are namely the EA treatment group and the control group. Figure 1 shows the flowchart, which describes the research flow in detail. In addition, the trial schedule of enrolment, treatments, and outcome assessments is shown in Table 1. The reporting of this protocol is based on the SPIRIT reporting guidelines (24).

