### Study procedure

The duration of the trial will include three study phases, including screening in the baseline phase (week 0), 4-week treatment phase (weeks 1–4), and follow-up phase (week 8). The qualification of prospective participants will be determined by researchers who will not be involved in the assessment or treatment. At the screening meeting, patients will be given more detailed information about the study procedures. Before the first treatment (baseline, week 0), after the last treatment (post-treatment, week 4), and in the fourth week of follow-up after treatment (week 8), all participants will be required to complete several questionnaires as the outcomes of the study to evaluate the curative effect, including EORTC QLQ-CIPN20 and EORTC QLQ-C30 questionnaires. The participants cannot take drugs that may influence the outcomes of the study during the trial, including pain drugs or unspecified CIPN-related therapeutic drugs. If the patient has to take drugs that will influence the outcomes of the study due to disease progression, the patient will be considered to have dropped out. To promote enrollment, all treatment costs and outcome measurements will be free for participants.

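### The stated two-sample tests name no baseline adjustment for CIPN20 and QLQ-C30; ANCOVA on the baseline score would be more precise at no cost in a trial of 35 per group

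*Protocol article*

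**What the plan says.** The between-group method stands in one place, the Statistical analysis section of the protocol article. It opens with "To compare the two independent samples" and says that the t-test "will be used to determine the numerical data of normal distribution, while the non-parametric test will be used" for data that are not normal. On the remaining outcomes it says: "The chi-square test or non-parametric tests will be used to determine categorical data". On error rates it says: "All hypothesis tests will be bilateral, with the level of significance established at 0.05". The section names no covariate, change score or repeated-measures model.

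The baseline values are available. The Abstract states "The results will be evaluated at baseline, post-treatment phase, and follow-up", and Study procedure and Table 1 agree: CIPN20, CTCAE grade and QLQ-C30 are each scheduled at week 0, week 4 and week 8.

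On size, the Sample size section says "35 patients will be included in each group", and Study design has patients "randomly divided into two groups in a ratio of 1:1". The Background calls the trial a pilot and explains that a larger or multicentre study is not feasible. The article gives no target effect, SD, power or correlation between visits.

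**The concern.** A symptom score before treatment usually predicts the same score a few weeks later. A comparison that leaves it out carries between-patient variation that the trial has already measured and could remove.

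Two features make this relevant here. First, the Background says that eligible patients are scarce, so the sample cannot readily be enlarged and efficient analysis is one of the few remaining ways to gain precision. Second, severity at entry can vary: Table 2 sets no minimum or maximum neuropathy grade, and the Discussion admits patients with sensory symptoms only while describing others with motor damage.

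The rule also lets the shape of the data decide between a t-test and a rank test, and gives no criterion for that decision. The summary being compared, a mean difference or a difference in ranks, is therefore settled only once data are seen. A single prespecified model would remove that step.

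**Working it through.** **Inputs from the article:** 35 per group, 1:1 allocation, two-sided 0.05, scores at baseline, week 4 and week 8.

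**Assumptions, not in the article:** rho, the correlation between baseline and follow-up score, shown from 0.3 to 0.8; equal SDs at the two visits; a linear relation; an illustrative true effect of 0.5 SD. There is no stated power or effect from which the sample size could be reproduced.

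**Step 1. Relative variance of the treatment difference**, with an unadjusted follow-up score set to 1:
- change score: 2(1 − rho)
- ANCOVA: 1 − rho²

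**Step 2. Precision lost relative to ANCOVA:**
- follow-up scores compared: 1 − (1 − rho²) = rho²
- change scores compared: 1 − (1 − rho²)/[2(1 − rho)] = (1 − rho)/2

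**Step 3. Power for 0.5 SD**, from the noncentral t distribution (68 df for the t-tests, 67 for ANCOVA). The noncentrality for follow-up scores is 0.5 × √(35/2) = 2.09. It is divided by √[2(1 − rho)] for change scores and by √(1 − rho²) for ANCOVA. At rho 0.7 these are 2.09/√0.60 = 2.70 and 2.09/√0.51 = 2.93.

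| rho (assumed) | Loss, follow-up scores | Loss, change scores | Power, follow-up | Power, change | Power, ANCOVA |
|---|---|---|---|---|---|
| 0.3 | 9% | 35% | 54% | 41% | 58% |
| 0.5 | 25% | 25% | 54% | 54% | 66% |
| 0.6 | 36% | 20% | 54% | 64% | 73% |
| 0.7 | 49% | 15% | 54% | 76% | 82% |
| 0.8 | 64% | 10% | 54% | 90% | 93% |

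**Step 4. Effect detectable with 80% power**, normal approximation: (1.960 + 0.842) × √(2/35) = 0.67 SD for follow-up scores. Multiplying by √(1 − rho²), ANCOVA gives 0.64, 0.58 and 0.48 SD at rho 0.3, 0.5 and 0.7. Change scores give 0.79, 0.67 and 0.52 SD at the same values.

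**Step 5. Equivalent sample size.** Against follow-up scores, ANCOVA with 35 per group is worth 35/(1 − rho²), which is 47, 55 and 69 per group at rho 0.5, 0.6 and 0.7.

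**Step 6. Small-sample check.** ANCOVA must estimate the baseline slope. In 20,000 simulated trials of 35 + 35, the loss from comparing follow-up scores was 8%, 24% and 48% at rho 0.3, 0.5 and 0.7, against 9%, 25% and 49% by formula. The cost of estimating the slope is about one percentage point.

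**The case against.** The strongest objection is that the size of the loss is unknown. No correlation appears in the article, and it could be low: the Discussion ties severity to accumulating dose, and the entry requirements on daily living ability and KPS may narrow the spread of baseline scores. At rho 0.3, ANCOVA raises power over follow-up scores only from 54% to 58%. The section also does not say whether the tested variable is the follow-up score or the change from baseline. If it is change, baseline is already used in part, and the loss shrinks as rho rises. Both points stand. A reader might infer that a quarter to a half of the precision is certainly thrown away; that needs rho of about 0.5 to 0.7 and a test on follow-up scores, neither of which is stated.

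A reader might also infer bias from chance baseline imbalance. That does not follow: randomization keeps the unadjusted test valid, and its standard error already allows for such imbalance. Nor does the article say that weeks 4 and 8 are analysed as unrelated or that randomization is unstratified; those are silences in a condensed account. The article states that analysts will not know the allocation, which limits any scope to pick a test that favours one arm. As a pilot without a power target, the trial does not miss a promised figure; the 0.5 SD effect only sets a scale.

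What the objection does not remove is the stated method itself. Two-sample tests are what the article specifies, so baseline adjustment would change that method and not merely fill in a detail. ANCOVA is the more precise choice under either reading at every rho in the table.

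**Conclusion.** The point holds as one of efficiency. For CIPN20 and QLQ-C30 the stated tests are valid but less precise than a baseline-adjusted analysis of data already being collected. The loss is 25% to 49% of the precision if follow-up scores are compared, or 25% to 15% if change scores are, at an assumed rho of 0.5 to 0.7. Over rho 0.3 to 0.8 the ranges are 9% to 64% and 35% to 10%. The direction is secure; the size depends on the unknown correlation and on the unstated analysis variable.

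The figures describe t-tests on continuous scores. They do not carry over to the rank tests or to the ordinal CTCAE grade, which is also listed as a primary outcome. The change is worth making, but the analysis as written is not invalid.

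**What to change.** For CIPN20 and QLQ-C30, replace the normal/non-normal test rule with one prespecified model: ANCOVA of the week-4 score on group and baseline score. A mixed model for weeks 4 and 8 with baseline and baseline-by-visit terms is an alternative that also keeps patients who miss one visit. Report the adjusted mean difference with its 95% CI, and keep a rank-based analysis, preferably baseline-adjusted, as a sensitivity check. CTCAE grade needs its own wording, for example an ordinal model with baseline grade.

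The cost is a few lines of analysis text, best settled before allocation is revealed to the analysts. The SPSS version named in the article can fit these models, and no new data or visits are needed.

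### The ordered CTCAE grade, a primary outcome, may be compared by chi-square or by a non-parametric test, with no rule for choosing and no use of the baseline grade

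*Protocol article*

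**What the plan says.** The abstract (Methods and analysis) names "the peripheral neurotoxicity assessment rating according to NCI CTCAE version 5.0" as a main outcome beside the QLQ-CIPN20, and the grade has its own subsection under Primary outcome. That subsection defines four grades of rising severity. For example, "Grade II includes moderate sensory numbness or sensory loss, which affects function but does not affect daily life", and at the top, "Grade IV includes sensory-motor neuropathy, which severely interferes with daily life".

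Table 1 schedules the grade at baseline, week 4 and week 8. The abstract agrees: "The results will be evaluated at baseline, post-treatment phase, and follow-up".

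Under Statistical analysis, the rule for such data is "The chi-square test or non-parametric tests will be used to determine categorical data", followed by "All hypothesis tests will be bilateral, with the level of significance established at 0.05". The only comparison described is of two independent samples. No adjustment for baseline and no change score is mentioned. The Sample size section states that "35 patients will be included in each group", without an effect size, power or expected grade distribution.

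**The concern.** A chi-square test on the group-by-grade table treats the grades as unordered labels. It spreads its power over every possible difference in pattern, although the hypothesis is that severity shifts downward. A rank test uses the order. The plan permits both and ranks neither, so two p-values are available for one primary outcome. Both also discard the baseline grade, which is likely to predict the week-4 grade.

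The stake is larger for this outcome than for the others. The Blinding section concedes that participants know their treatment, and both questionnaires are completed by participants. The CTCAE grade is set by a professional evaluator, and outcome assessors are to be kept unaware of allocation. It is therefore the trial's best protection against expectation effects, and the sample is fixed at 35 per group.

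**Working it through.** **Inputs from the article.** 35 per group; 1:1 allocation; two-sided 0.05; ordered grades I to IV; grade recorded at baseline, week 4 and week 8; chi-square or a non-parametric test for categorical data.

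**Assumed, because the article gives none.** Grade distribution, size of shift, baseline correlation, and whether a fifth level (neuropathy resolved) occurs. All power figures below are simulations under these assumptions, with 3,000 to 4,000 trials per setting where the count is recorded.

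**Step 1: the plan's own figure.** The 35 per group cannot be reproduced, as no effect size or power is stated. For scale, the standardized difference detectable with 80% power is (1.960 + 0.842) × √(2/35) = 2.802 × 0.239 = 0.67. Shifts of 0.5 to 0.7 SD are therefore a relevant range.

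**Step 2: cost of ignoring order.** Pearson chi-square against the Wilcoxon-Mann-Whitney test, under a proportional-odds shift:

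| Assumed control distribution | OR | Chi-square | Rank test | Loss (points) |
|---|---|---|---|---|
| Three levels: 0.30/0.45/0.25 | 2 | 25.8% | 33.6% | 7.8 |
| | 3 | 55.1% | 65.1% | 10.0 |
| Four levels: 0.25/0.40/0.30/0.05 | 2 | 21.3% | 34.2% | 12.9 |
| | 3 | 51.3% | 69.1% | 17.8 |
| Five levels: 0.10/0.30/0.35/0.20/0.05 | 2 | 18.5% | 33.8% | 15.3 |
| | 3 | 45.7% | 69.9% | 24.2 |

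The loss runs from about 8 to 25 points and grows with the number of occupied levels.

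**Step 3: cost of ignoring baseline as well.** Baseline and week-4 grades were cut from a bivariate normal with correlation 0.6. The adjusted analyses were a baseline-adjusted rank test and the proportional-odds model logit P(Y ≤ j) = α_j − β·group − γ·baseline grade. Ranges across settings:

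| Latent shift | Chi-square | Rank test | Adjusted rank test | Proportional odds |
|---|---|---|---|---|
| 0.5 SD | 29–34% | 45–49% | 56–61% | 54–63% |
| 0.7 SD | 52–61% | 71–77% | 81–88% | 85–87% |

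One setting in full (five levels, cut-points −1.2, −0.2, 0.9, 2.0):
- At 0.5 SD the powers are 28.6%, 47.7% and 61.4% for chi-square, rank and adjusted rank. Chi-square loses 47.7 − 28.6 = 19.1 points to the rank test and 61.4 − 28.6 = 32.8 to the adjusted test. The rank test loses 61.4 − 47.7 = 13.7.
- At 0.7 SD they are 54.6%, 76.5% and 88.0%, giving losses of 21.9, 33.4 and 11.5.

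The gain from baseline depends on the correlation. With four grades and a 0.5 SD shift, moving from the rank test to rank ANCOVA adds 54.6 − 47.6 = 7.0 points at correlation 0.5, 67.6 − 47.8 = 19.8 at 0.7 and 75.5 − 46.6 = 28.9 at 0.8.

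**Step 4: cost of the open choice.** With no effect, each test alone rejected in about 4 to 6% of trials. Counting a trial as positive if either chi-square or the rank test was significant gave about 6 to 9%, below the ceiling of 0.05 + 0.05 = 10%. With a real effect and five levels, the two tests disagreed on significance in about 25% of trials.

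**Step 5: sparse cells.** With four or five levels, at least one expected count was below 5 in 89 to 100% of tables; with three occupied levels, in 1 to 27%. Sparseness did not inflate the chi-square test's error rate. The loss in Steps 2 and 3 comes from ignoring order and baseline.

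**The case against.** The best reply is that the plan never assigns chi-square to the grade. The same sentence permits non-parametric tests, and a natural reading is chi-square for nominal variables and rank tests for ordinal ones. This stands: a reader might infer that the primary grade is bound to the weakest test, and the text does not say so. It does not say the opposite either, and the rank test still leaves baseline unused.

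A second reply is that the choice of test and covariates is normally left to an analysis plan, which is not shown, and that this is a condensed article on a pilot study. That limits the point but does not remove it. The article does not defer the matter; it states a rule, and the rule leaves a primary outcome without a determined test.

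Third, the analysts are to be blinded to allocation, and the Discussion names only the QLQ-CIPN20 as the main outcome, using the grade as an accuracy check. Blinding does limit choosing a test to favour an arm, so the 6 to 9% describes what the open rule permits and not a forecast. It does not tell the analyst which result is primary. The Discussion does not remove the grade from the Primary outcome section.

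Fourth, the sparseness depends on the assumed distribution. The Discussion says patients with sensory symptoms only will be included, while grade IV is sensory-motor, so three occupied grades are plausible. This is accepted, and sparseness carries no weight in the conclusion.

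**Conclusion.** The point holds as an undetermined and inefficient analysis of a primary outcome. It is not an invalid one, since each permitted test keeps its error rate near 5%. Under the stated assumptions (35 per arm, three to five occupied categories, correlation 0.6, shift 0.5 to 0.7 SD), chi-square gives up about 10 to 25 points of power to a rank test and about 20 to 35 to a baseline-adjusted ordinal test. The unadjusted rank test gives up about 10 to 15. None of these figures comes from the article, and the gain from baseline shrinks if the correlation is lower.

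A reader might summarize this as chi-square halving the power. That is not general. In the five-level setting chi-square keeps 28.6/61.4 = 47% of the adjusted test's power at 0.5 SD but 54.6/88.0 = 62% at 0.7 SD. Against the permitted rank test it keeps 28.6/47.7 = 60% and 54.6/76.5 = 71%.

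**What to change.** Add one sentence naming a single primary analysis of the week-4 CTCAE grade, with a category for no neuropathy because the four defined grades have no place for a patient whose symptoms resolve. Use either proportional-odds regression on group and baseline grade, reporting the common odds ratio with its 95% CI, or a baseline-adjusted rank test. If one is to be a fallback for the other, write down the trigger before unblinding; otherwise the open choice returns in another form. Keep chi-square or Fisher's exact test for unordered variables only.

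The cost is the sentence itself. The grade is already collected at baseline, SPSS fits ordinal regression, and no extra patient or visit is needed. The downside is reliance on the proportional-odds assumption, which the baseline-adjusted rank test avoids at the price of a less interpretable effect measure.
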